### Data collection and follow-up period

The primary outcome measure would be the HAMD-17 score on the third postoperative day. Secondary study indicators include (1) the visual analog scale (VAS) and HAMD-17 scores prior to surgery, immediately after entering the PACU, and 1, 2, 3, 4 and 5 days after operation; (2) RASS score when the patient enters the operating room and at 1, 2, 3, 4 and 5 days after surgery; (3) the dosage of sufentanil and esketamine after surgery; (4) postoperative analgesia pump press times, rescue analgesia times, rescue drug dosage, and number of rescue analgesia times and rescue drug dosages at 6, 24, 48, and 72 h after the patient entered the PACU; (5) postoperative complications and adverse events; (6) postoperative hospital stay; (7) concentrations of brain-derived neurotrophic factor (BDNP), 5-hydroxytryptamine (5-HT), tumor necrosis factor (TNF-α), and interleukin-6 at 1, 3, and 5 days post-surgery; and (8) the patient survival rate at 6 and 12 months post-surgery. The intervention is self-regulated, and the authors are monitoring usage. Nurses in the ward will be responsible for assisting in the follow-up study of medication to ensure patient compliance. Implementing the esketamine or control group will not require alteration to usual care pathways (including the use of any medication), and these will continue for both trial arms.

Safety end-point measures will include incidence, severity, and causality of reported serious adverse events (SAEs), namely changes in the occurrence of the expected common prematurity complications and clinical laboratory test assessments, and the development of unexpected SAEs in this high-risk population. All SAEs will be followed until a satisfactory resolution or until the investigator responsible for the care of the participant deems the event to be chronic or the patient to be stable. All expected and unexpected SAEs, whether or not they are attributable to the study intervention, will be reviewed by the principal investigator and all authors to determine if there is a reasonable suspected causal relationship to the intervention. If the relationship is reasonable, SAEs will be reported to the Ethics Committee to guarantee the safety of participants.

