**Methods/design:**

This prospective, single-center, randomized control trial will include 80 patients who will undergo elective PD. The patients will be randomly assigned to two groups: the experimental group that will receive esketamine (*n* = 40) and the control group (*n* = 40). In the esketamine group, the analgesic pump will be connected immediately after surgery. A solution of esketamine 1.5 mg/kg + sufentanil 2 µg/kg, diluted to 150 mL, will be administered continuously for 72 h at the background infusion and impact doses of 1 mL/h and 2 mL/time, respectively; the locking time will be 10 min. The control group will receive sufentanil 2 µg/kg that will be administered as per the esketamine group. The primary outcome will be the Hamilton Depression Scale (HAMD-17) score on the third day post-surgery (POD3). Secondary study indicators will include (1) visual analog scale (VAS) score and HAMD-17 score prior to surgery, immediately after entering the postanesthesia care unit (PACU) and 1, 2, 3, 4, and 5 days after surgery; (2) Richmond Agitation-Sedation Scale (RASS) score at 1, 2, 3, 4, and 5 days after surgery; (3) consumed doses of sufentanil and esketamine after surgery; (4) postoperative analgesia pump effective press times, rescue analgesia times, and rescue drug dosage, recording the number of rescue analgesia and rescue drug dosage at 6, 24, 48, and 72 h after the patient enters the PACU; (5) postoperative complications and adverse events; (6) postoperative hospital stay; (7) concentrations of brain-derived neurotrophic factor (BDNP), 5-hydroxytryptamine (5-HT), tumor necrosis factor (TNF-α) and interleukin-6, at 1, 3, and, 5 days post-surgery; and (8) the patient survival rate at 6 and 12 months post-surgery.

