### Statistical methods

Statistical analysis will be carried out using the “intention to treat” method; all data will be collected in a single database and analyzed to evaluate any differences between the randomized groups for both primary and secondary outcomes. SAS 9.4 (SAS Institute, Cary, NC, USA) statistical software will be used for all statistical analysis. All statistical tests are two-tailed. *P*-values ≤ 0.05 will be considered statistically significant. Normally distributed data will be described as mean ± standard deviation, and the analysis of variance will be used for comparison between groups. Non-normally distributed data will be described as median (minimum–maximum), and the rank-sum test will be used for comparison between groups. The counting data are statistically described by frequency (composition ratio), and the *χ*^2^ test or exact probability method will be used for comparison between groups. The rank-sum test will be used for the inter-group comparison of grade data.

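### Pre-operative HAMD-17 and VAS are listed as secondary outcomes instead of serving as baseline, and every outcome gets an unadjusted two-group test at P ≤ 0.05

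*Protocol article*

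**What the plan says.** The Data collection and follow-up period section names one primary outcome, the HAMD-17 score on postoperative day 3. Its secondary list includes VAS and "HAMD-17 scores prior to surgery, immediately after entering the PACU, and 1, 2, 3, 4 and 5 days after operation". It also includes RASS on entry to the operating room and on days 1 to 5, four serum markers on days 1, 3 and 5, the number and dose of rescue analgesics at four times, and survival at two times.

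The Methods/design part of the abstract says of the esketamine group that "the analgesic pump will be connected immediately after surgery", and that the control infusion is given in the same way. No study drug is therefore on board at the pre-operative or operating-room assessment.

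Under Statistical methods, all data will be "analyzed to evaluate any differences between the randomized groups for both primary and secondary outcomes". For normally distributed data, "the analysis of variance will be used for comparison between groups"; for other continuous data, "the rank-sum test will be used for comparison between groups". Counts get a chi-square or exact test, and graded data a rank-sum test. One rule covers everything: "All statistical tests are two-tailed", and P-values "≤ 0.05 will be considered statistically significant". The section names no baseline covariate and no model across days, and does not say how secondary P-values are to be read.

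**The concern.** Two things are poorly fixed.

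First, pre-operative HAMD-17 and VAS are placed among the outcomes. In a randomised trial, a between-group test of a pre-treatment value can only detect a chance imbalance. The useful role of such a value is as a covariate. The scores are already collected, and the stated tests make no use of them.

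Second, the stated hypothesis (Discussion, and the abstract) spans HAMD-17, VAS, adverse reactions and four markers, and names no time point. With one threshold for primary and secondary outcomes alike, a single favourable day on a single scale could be presented as support. The article gives readers no way to tell such a result from a planned, confirmatory one.

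**Working it through.** The plan states neither a count of secondary tests nor a chance-positive rate, so it has no figure of its own to reproduce here. The inputs below come from the Data collection and follow-up period section and the abstract.

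**Count of post-surgery secondary comparisons, one per outcome and time point**

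- HAMD-17: PACU entry and days 1, 2, 4, 5 (day 3 is the primary) = 5
- VAS: PACU entry and days 1 to 5 = 6
- RASS: days 1 to 5 = 5
- Biomarkers: 4 markers × 3 days = 12
- Rescue number and rescue dose: 2 × 4 times = 8
- Pump presses = 1
- Sufentanil dose = 1 (esketamine dose is not comparable, because controls receive none)
- Complications and adverse events, counted once = 1
- Hospital stay = 1
- Survival: 2 times = 2

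Total: 5 + 6 + 5 + 12 + 8 + 1 + 1 + 1 + 1 + 2 = 42. The first four lines give 5 + 6 + 5 + 12 = 28.

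Pump presses count once because the abstract ties the 6, 24, 48 and 72 h times to the rescue measures only. If presses were also tested at all four times, the total would be 42 + 3 = 45. The three pre-drug comparisons (HAMD-17 and VAS before surgery, RASS on entering the operating room) are left out of the 42.

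**Chance positives if the drug affects none of these outcomes**

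The expected number is k × 0.05, whatever the correlation. The probability of at least one is 1 − 0.95^k if the tests are independent.

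| Comparisons counted | k | Expected | At least one (independent) |
|---|---|---|---|
| All post-surgery secondaries | 42 | 2.10 | 0.884 |
| Without the two PACU-entry tests | 40 | 2.00 | 0.871 |
| HAMD-17, VAS, RASS, biomarkers only | 28 | 1.40 | 0.762 |
| Presses tested at four times | 45 | 2.25 | 0.901 |

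For jointly normal two-sided test statistics, independence is the upper case (Šidák's inequality), so 0.884 is a ceiling for the 42.

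**Effect of correlation**

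The documents give no correlations, so these are assumed: 0.3 to 0.8 between test statistics within a family of repeated measures, and 0 to 0.3 between families. A simulation of 200,000 draws used 45 comparisons, made up of these 42 plus the three pre-drug ones. The probability of at least one chance positive was about 0.66 to 0.88, against 0.90 under independence. The 42 are a subset, so under the same correlations their probability is no higher.

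**What a baseline covariate gains**

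Adjusting a day's score for its pre-operative value multiplies the residual variance by about 1 − ρ², where ρ is the within-group correlation between the two scores. The documents give no ρ, so the gain cannot be sized.

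**The case against.** The strongest reply is that Statistical methods is a generic paragraph matching tests to data types. It never says that each time point is tested separately or that pre-operative scores will be compared for efficacy. A longitudinal model and the handling of secondary multiplicity are often left to the full protocol or SAP, neither of which is shown. HAMD-17 and RASS are also assessed before surgery as part of entry evaluation (Inclusion criteria). This stands in part. Day-by-day testing is the natural reading, but it is inferred, and the absence of a formal multiplicity procedure is not an error here. What remains is what the article does state: unadjusted two-group methods, one threshold for primary and secondary outcomes, and pre-drug values listed as outcomes.

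Three further points on that side are sound:

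- A single-day comparison uses one observation per patient and keeps its nominal error rate. A reader might infer that ignoring within-patient correlation makes these tests invalid. It does not; the issue is efficiency and clarity.
- The Sample size calculation section provides for multiple imputation, which partly answers any worry about patients who miss a given day.
- The article already names one primary outcome at one time point. A reader might infer that dozens of secondary tests inflate its error rate. They do not.

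**Conclusion.** The point holds as an improvement worth making. The article's stated methods leave collected baseline scores unused, class three pre-drug measurements as outcomes, and allow about 42 secondary comparisons to be called significant at the primary's threshold. About 2 of those would be expected by chance.

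This rests on one test per outcome and time point, pump presses and complications each counted once, and no true effect on any secondary outcome.

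A reader might infer that a chance positive is close to certain. The figures do not support that: the ceiling is about 88%, and under the assumed correlations the probability could be nearer two thirds. Nor do all the comparisons come from the repeated scales and markers, which supply 28 of the 42. The concern is how secondary results will be read; the validity of the primary test is not in question.

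**What to change.** - **HAMD-17 and VAS.** Fit one mixed model for repeated measures per scale, with treatment, day, treatment-by-day and the pre-operative score as covariate. Take the primary day 3 HAMD-17 contrast from this model.
- **Biomarkers.** No pre-operative sample is listed, so fit the same model without a baseline term. With complete data, this mainly replaces three daily tests per marker with one stated contrast.
- **Contrasts.** Name one contrast per secondary repeated outcome before unblinding, and give daily estimates with 95% confidence intervals. Choose the days deliberately: an average over days 1 to 5 mixes days during and after the 72 h infusion and, for HAMD-17, contains the primary day.
- **Pre-drug and PACU-entry values.** Use pre-operative scores as baseline and do not test them between groups. Treat RASS on entering the operating room likewise. Report PACU-entry scores descriptively.
- **Labelling.** State that secondary P-values are exploratory.

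One contrast each for HAMD-17, VAS and four markers replaces 5 + 6 + 12 = 23 comparisons with 6, so the 42 fall to 42 − 23 + 6 = 25, with 25 × 0.05 = 1.25 chance positives expected. RASS, an ordinal grade, can keep its rank-sum comparisons under the exploratory label.

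No new data are needed, and SAS 9.4 is already planned. The cost is slightly more programming and fewer secondary results that can be called significant. If the SAP already contains such a model, only the article's text needs to be brought into line.

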### Dropout criteria

(1) Patients who voluntarily withdraw their informed consent at any time during the study; (2) failure to complete treatment as planned or refusal of postoperative neuropsychological evaluation; (3) any clinical adverse event or other medical condition in which the continued use of the drug may no longer benefit the subject; (4) lack of main indicators and obvious incomplete data; (5) the efficacy will not be evaluated for cases removed from the group because of adverse reactions, but the adverse effects of treatment should be included in the statistics; and (6) other reasons that the investigators believe may justify the discontinuation of the trial.

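### Pump sufentanil and press counts have no time base, so early pump stops can resemble opioid sparing, and the text conflicts on whether patients removed for adverse reactions are analysed

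*Protocol article*

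**What the plan says.** All references are to the protocol article.

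- **Outcomes.** Data collection and follow-up period lists "the dosage of sufentanil and esketamine after surgery; (4) postoperative analgesia pump press times". The Methods/design part of the Abstract has "consumed doses of sufentanil and esketamine after surgery; (4) postoperative analgesia pump effective press times". Neither wording gives a time window or refers to how long the pump ran.
- **Rescue.** This is listed separately and does have fixed times: "number of rescue analgesia times and rescue drug dosages at 6, 24, 48, and 72 h after the patient entered the PACU". It is not combined with the pump dose.
- **Pump.** The Abstract's settings are a solution "diluted to 150 mL, will be administered continuously for 72 h", with "background infusion and impact doses of 1 mL/h and 2 mL/time, respectively; the locking time will be 10 min". Both arms have 2 µg/kg of sufentanil in the pump.
- **Early stopping.** Dropout criteria, item (3), foresees "any clinical adverse event or other medical condition in which the continued use of the drug may no longer benefit the subject". Item (2) adds failure to complete the planned treatment. Item (5) says that efficacy is not assessed in cases removed for adverse reactions, although their adverse effects are still counted.
- **Analysis.** Statistical methods specifies intention to treat and says that "all data will be collected in a single database and analyzed to evaluate any differences between the randomized groups for both primary and secondary outcomes".
- **Missing data.** Sample size calculation provides for multiple imputation and assumes 5% overall withdrawal.

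**The concern.** One secondary aim is to learn how esketamine combined with sufentanil affects postoperative analgesia. Low sufentanil use and few presses will naturally be read as good analgesia; the pilot described under Treatment implementation used press and rescue frequencies in that way. But both quantities accrue only while the pump is connected. Once it stops they freeze, and later pain shows up in the rescue outcome instead. If more esketamine patients stop early, that arm's pump totals fall without any analgesic benefit.

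Multiple imputation does not help, because a truncated total is an observed value and not a missing one.

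The text then gives two answers on who is analysed. Statistical methods keeps everyone in the randomised comparison, truncated totals included. Dropout criteria, item (5), takes out those removed for adverse reactions, so the groups compared are partly defined by who tolerated treatment. One route risks truncation bias and the other selection bias.

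**Working it through.** **The plan's own figures.** The article states no expected value for presses or sufentanil use, so there is none to reproduce here. The sample size concerns a depression response rate: 10% v 40% with continuity correction gives 38 per arm, and 76/0.95 = 80. This point does not touch it.

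**Inputs from the article.** 2 µg/kg sufentanil in 150 mL; background 1 mL/h; bolus 2 mL; planned duration 72 h. The concentration is 2/150 = 0.0133 µg/kg per mL.

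**Step 1: pump time alone drives the total.** Sufentanil from background infusion, with no presses at all:

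- full 72 h: 72 × 2/150 = 0.96 µg/kg
- stopped at 48 h: 48 × 2/150 = 0.64 µg/kg
- stopped at 24 h: 24 × 2/150 = 0.32 µg/kg

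The total falls by two thirds for a stop at 24 h, whatever the pain.

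**Step 2: effect on the arm mean.** Suppose both arms have the same hourly use, and a fraction p more of the esketamine arm stops at hour t. The spurious relative reduction in mean pump sufentanil and mean presses is p × (1 − t/72). The values of p and t are assumptions.

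| Excess stops p | t = 24 h (p × 0.667) | t = 12 h (p × 0.833) |
|---|---|---|
| 5% | 3.3% | 4.2% |
| 10% | 6.7% | 8.3% |
| 20% | 13.3% | 16.7% |

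**Step 3: effect on the test.** A simulation with 40 per arm, equal analgesic need, and a two-sided rank-sum test at 0.05 on total pump sufentanil. Assumptions not in the article: a mean of 15 boluses over 72 h, between-patient coefficient of variation 0.6, stop times uniform between 6 and 72 h and unrelated to need, and stops in the esketamine arm only.

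| Stops, esketamine arm | False mean saving (µg/kg) | Type I error, raw total |
|---|---|---|
| 0% | 0 | 5% |
| 5% | 0.03 | 6% |
| 10% | 0.06 | 8% |
| 20% | 0.12 | 25% |
| 30% | 0.18 | 48% |

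Cross-check: the expected full total is 0.96 + 15 × 2 × 2/150 = 1.36 µg/kg, and the mean stop time is (6 + 72)/2 = 39 h. At p = 20% the formula gives 0.20 × (1 − 39/72) × 1.36 = 0.12, as simulated. With 20% stops in both arms the type I error is 5%, so the distortion needs an imbalance in stopping.

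**Step 4: the alternative rule.** Excluding the stopped patients kept the type I error between 4% and 5% in the same simulation, but only because stopping was made independent of need. If patients who stop differ in their need for analgesia, exclusion is not neutral.

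**The case against.** **The adverse-event patient may not be counted at all.** Item (5) of the dropout criteria would take a patient removed for intolerance out of the efficacy evaluation. A reader might infer that the plan scores such a patient as having the best analgesia; the article does not settle that. This part of the objection stands. What remains is the conflict with the intention-to-treat statement, and the narrow reach of item (5): it covers only cases removed for adverse reactions. It does not say what happens to totals from pumps stopped for other reasons, or from patients who stay in the trial after stopping.

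**The lack of a time base is silence.** The article lists what is collected, and handling of early stops may be set out in the full protocol or an analysis plan, neither of which is shown. That is fair, and it limits the weight of the point. The conflict between the two stated rules is in the article itself.

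**The size is modest.** The only related figure is 5% withdrawal, or 0.05 × 80 = 4 patients. If all four were esketamine patients stopping at 24 h, that is 4/40 = 10% of the arm and a 6.7% spurious reduction. Nothing in the article supports stop rates of 20–30%. Lost analgesia would also be visible in rescue use, pain scores and adverse events, all already collected, and the stated hypotheses make no opioid-sparing claim. All of this stands, so a reader should not conclude that the endpoint's meaning is reversed.

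**An emptied pump is not the same problem.** A reader might infer that a pump that runs dry also mimics good analgesia. It does not. It has delivered the full 2 µg/kg, the highest total possible. Delivered boluses when it empties at hour t are (150 − t)/2: 39 at 72 h, 51 at 48 h, 63 at 24 h. So 39 is the minimum for a pump that empties within 72 h, not a cap on presses. A volume ceiling shrinks real differences: with an assumed mean need of 30 v 40 boluses, the simulated gap is 0.11 µg/kg with the ceiling and 0.26 without. With equal need, the type I error stays at 5%.

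**Conclusion.** The point holds in a limited, conditional form. As worded, pump sufentanil and presses carry no time base and are kept apart from rescue, so unequal early stopping can produce an apparent sparing effect if intention to treat governs. If item (5) governs instead, the comparison depends on tolerance. The article supports both readings, and they must be reconciled.

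The distortion is small near the stated withdrawal rate and becomes serious only at about 20% excess stops or more. It rests on assumed stop rates and times, on stopping being more frequent with esketamine, and on equal hourly use otherwise. Severity is minor.

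**What to change.** - **Redefine the opioid outcome** as total opioid over 0–72 h: pump sufentanil plus any rescue opioid, in one unit with a conversion fixed in advance. Collect it in every randomised patient whether or not the pump is still running. The rescue drug is not named in the text shown; a non-opioid rescue drug would need its own line. Values that are truly missing can then go to the planned multiple imputation.
- **Reconcile item (5) of Dropout criteria with Statistical methods**, stating which patients enter the efficacy comparison. For this outcome, keeping all randomised patients avoids both truncation and selection.
- **Record pump stop time and reason**, and report both by arm beside the opioid result.
- **Presses per connected hour should be supplementary at most.** In the simulation it kept the type I error at 4–6%, but it conditions on pump time after randomisation. If use is heavier early after surgery (an assumption), it would inflate the rates of early stoppers.

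The cost is a change of outcome wording, one recorded time with its reason, and a prespecified conversion. Pump and rescue doses are already collected.

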### Sample size calculation

The clinically meaningful beneficial effect of esketamine on the depressive symptoms of patients undergoing surgery is unclear. The minimum clinically important difference was at least 20%; however, differences in response rates range from approximately 26 to 56% among patients with major depressive disorder [17]. Therefore, we assumed that for surgical patients, the third postoperative day response rate difference would be 30% between the two groups. Likewise, for the control group, a response rate of 10% was assumed. A total of 38 patients in each group would provide 80% power with a two-sided type-I error of 0.05. The test-group-to-control-group ratio is 1. Considering an overall withdrawal rate of 5%, a sample size of 80 patients is considered adequate [10]. If data are missing, we will use multiple imputation methods to fill in according to the research needs.

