## Background

Pancreatoduodenectomy (PD) is the standard surgical procedure for the treatment of precancerous lesions and some benign conditions in the pancreatic head, distal bile duct, ampulla, and duodenum. It is traumatic, difficult to perform, and has a high incidence of postoperative complications and perioperative mortality. Postoperative complications and pain occur frequently and affect the psychological status of patients. Patients who have undergone PD often experience symptoms of anxiety and depression. Studies have shown that the incidence rates of anxiety and depression in such patients are approximately 33.6 and 27.6%, respectively [1, 2]. Additionally, patients have high postoperative pain scores over a long duration, and their pain is difficult to treat [3]. The untimely treatment of postoperative depression and incomplete analgesia can prolong the hospital stay of patients and increase the incidence of complications and treatment costs, and postoperative pain may aggravate their symptoms of postoperative depression [1]. Therefore, more drugs and accurate models are needed to meet the urgent clinical demands of patients with intractable visceral pain.

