### Exclusion criteria

(1) Opioid analgesics were administered before surgery; (2) drug use or alcohol or drug abuse; (3) patients with preoperative cognitive impairment based on a Mini-Mental Scale Exam scale (normal cut-off value: > 23 points); (4) history of severe cerebrovascular disease; (5) mental illness, patients with a clear diagnosis of depression and long-term drug treatment; (6) no written informed consent for the study and/or no acceptance to have PD surgery; (7) sensitivity to esketamine and related drugs; (8) previous contraindications to ketamine use (e.g., severe refractory hypertension, cor pulmonale, hyperthyroidism, epilepsy, increased intraocular pressure, increased intracranial pressure, intracranial space-occupying lesions, and a history of cerebrovascular accidents); and (9) the investigator thinks that the patient should not participate in this trial.

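### The 80% power is stated for a response-rate difference extrapolated from patients with major depressive disorder, not for the HAMD-17 score that is the primary outcome in a trial excluding diagnosed depression

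*Protocol article*

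**What the plan says.** The Sample size calculation section of the protocol article admits that the worthwhile effect in surgical patients is not known. It gives a minimum important difference of at least 20%, reports that "differences in response rates range from approximately 26 to 56% among patients with major depressive disorder", and draws its assumption from there: "we assumed that for surgical patients, the third postoperative day response rate difference would be 30% between the two groups". It adds that "for the control group, a response rate of 10% was assumed", without naming a source population. The result is "A total of 38 patients in each group would provide 80% power with a two-sided type-I error of 0.05", raised to 80 in total for 5% withdrawal.

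Four other places bear on this:

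- **Exclusion criteria**, item 5: "mental illness, patients with a clear diagnosis of depression and long-term drug treatment".
- **Inclusion criteria**: HAMD-17 is measured before surgery, but no minimum score is required.
- **Data collection and follow-up period**: the primary outcome is the HAMD-17 score on the third postoperative day. Response is not listed as an outcome and is not defined in the text shown.
- **Background**: among patients who have had pancreatoduodenectomy, "incidence rates of anxiety and depression in such patients are approximately 33.6 and 27.6%, respectively".

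**The concern.** Two links in the planning argument are weak.

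The first is the population. A response rate in major depressive disorder describes people who begin with substantial symptoms. This trial sets out to leave such patients out and asks for no symptoms at entry, so many participants may have little to improve on. Nothing in the section explains why a 30-point difference should carry over, and the 27.6% in the Background is not reconciled with a 40% response.

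The second is the outcome. Power for a comparison of two proportions says nothing direct about power for a comparison of scores. The score analysis depends on the SD of HAMD-17 and on the mean difference expected, and the section gives neither.

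What is at stake is the reading of the result. If the trial finds no difference, a reader who trusts the 80% may take this as good evidence that esketamine has no worthwhile effect on mood, when the stated power does not refer to that analysis.

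**Working it through.** **Inputs.** Control response 10%, difference 30 points (hence 40% on esketamine), two-sided alpha 0.05, power 80%, 1:1 allocation, 38 per arm, 5% withdrawal: all from Sample size calculation. Depression rate 27.6%: from the Background.

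**1. The plan's own figure.** The mean of the two rates is 0.25.

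n = [1.960 × √(2 × 0.25 × 0.75) + 0.842 × √(0.10 × 0.90 + 0.40 × 0.60)]² / 0.30² = 31.5, so 32 per arm without continuity correction.

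With continuity correction: (31.5 / 4) × [1 + √(1 + 4 / (31.5 × 0.30))]² = 37.9, so 38 per arm.

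Withdrawal: 38 / 0.95 = 40 per arm, 80 in total. The plan's figures are reproduced. Exact power at 38 per arm, by enumerating all binomial outcomes, is 83% (Fisher) or 89% (uncorrected chi-square).

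**2. The assumption beside the 27.6%.** The answer depends on what response means.

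- *Improvement in a depressed patient, counted over all patients.* At most 27.6% of an arm can respond, which is below 40%.
- *Not depressed on day 3.* A 10% control rate means 90% depressed. With 27.6% depressed among controls, the control rate would be 72.4% and the largest possible gain 27.6 points, below 30.
- *A relative fall from the patient's own baseline, counted in everyone.* The 27.6% sets no ceiling, and 40% is possible.

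**3. Illustration of the dilution.** Let s be the share of patients able to respond (an assumption) and apply 10% against 40% within that share. Over all patients the rates become 0.10 × s and 0.40 × s. Exact power at 38 per arm:

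| s | Control | Esketamine | Fisher | Chi-square |
|---|---|---|---|---|
| 27.6% | 2.8% | 11.0% | 11% | 31% |
| 50% | 5% | 20% | 38% | 55% |
| 75% | 7.5% | 30% | 65% | 75% |
| 100% | 10% | 40% | 83% | 89% |

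A limiting case is 10% in controls with every depressed patient on esketamine responding, that is 10% against 27.6%. Power is then 41% (Fisher) or 52% (chi-square).

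**4. What 38 per arm supports for the score.** The normal approximation gives a detectable standardised difference of (1.960 + 0.842) × √(2 / 38) = 0.64. With the t distribution it is 0.65. This is the detectable mean difference in units of the HAMD-17 SD: every point of SD adds 0.65 points to it. The document gives no SD, so it cannot be turned into HAMD-17 points here.

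**The case against.** The sponsor has a fair reply. The section says openly that the effect in surgical patients is unclear, takes a value near the lower end of the 26 to 56% range, and does not claim that results in major depressive disorder apply unchanged. The exclusion wording is ambiguous: it may remove only diagnosed depression under long-term drug treatment, leaving patients with undiagnosed or milder symptoms eligible. No baseline HAMD-17 distribution is given, so nobody can say from the document how many participants have symptoms. All of this stands, and it limits how strongly the point can be put.

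A reader might go further and infer that 10% against 40% cannot occur. The document does not support this. It holds only under the first two meanings of response above, and the text shown gives no definition. The 27.6% is also an approximate rate from cited studies of patients after this operation. It does not measure the share of this sample able to respond on day 3.

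A reader might also infer that both rates were taken from major depressive disorder. Only the range of differences is tied to that population. The 10% is simply assumed, and the 40% is 10% plus 30 points.

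The reply does not rescue the statement as it stands. Under the relative-fall reading, a proportional drop from a near-normal score is still not the response observed in major depressive disorder, so the 30 points remain unsupported. Nor does any reading turn power for a response rate into power for the score.

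**Conclusion.** The point holds as a defect in the planning statement. The stated 80% rests on a difference extrapolated from a population that the trial largely excludes, and it refers to an undefined response rate and not to the declared primary outcome. The sample-size arithmetic is correct.

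The assumption is implausible beside the protocol's own 27.6%, and impossible only under the restrictive definitions of response. The dilution table is conditional on an assumed share able to respond. It shows how far the claim depends on that share: from 11% to 83% (Fisher) or 31% to 89% (chi-square).

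These figures should not be read as the power of the primary analysis. That analysis compares scores across all randomised patients, and its power cannot be computed without an SD and an expected difference. For the same reason, a floor effect on HAMD-17 is a reasonable worry but is not shown by the document.

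**What to change.** Stop presenting the response difference from major depressive disorder as the basis of 80% power for the primary outcome. Restate planning for the HAMD-17 score on the third postoperative day, for example: 38 evaluable patients per arm give 80% power to detect a standardised difference of about 0.65 (two-sided 0.05, t-test, equivalent to the planned analysis of variance with two groups). Convert this to HAMD-17 points with the SD pooled over both arms from patients already enrolled, without unblinding, and say whether a difference of that size is worth detecting. The blinded SD runs slightly high if there is a treatment effect: with a true standardised difference of 0.65 the factor is √(1 + 0.65² / 4) = 1.05.

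The cost is a rewritten paragraph and one blinded data summary. The stated power will probably look less favourable. The number of patients and the primary outcome stay as they are.
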